##### Peer Worker Training and Supervision

Peer workers will be trained by the research team to use the workbook *Targeting Employment for Emerging Adults: A Toolkit for Mental Health Providers* [76]. The workbook was developed and examined in previous research and provides a resource for providers to support emerging adult skill building [76]. It targets both educational and vocational training or attainment—the inclusion of both is vital to working with emerging adults. This workbook was selected for the proposed project because of its (1) specific focus on emerging adults, (2) portability and ease of use, (3) structure, and (4) ability to personalize to a given emerging adult. The workbook covers a range of topics relevant to vocational or educational skills. There is a combination of instructions for providers, informational handouts for emerging adults, and worksheets to support progress. While it was designed for an outpatient mental health setting, it can be easily used in other settings, and the training has been developed with input from individuals with lived experience in SU recovery (grant K23DA048161). Peer workers will receive supervision from the research team at least twice a month that may include reviewing adherence tools adapted as part of the project.

### Protocol

#### Aim 1: Adaptation of Training Protocols

##### Overview

Members of our team have trained various providers (clinicians, probation officers, and students) in different versions of CM (including CM-EA) and other SU services over the past 15 years. As a result, we have established multifaceted training protocols to train and support diverse providers to deliver SU services with high adherence. To ensure that the materials fit the scope of the current project, we will adapt our training protocols to allow for virtual training and support of *Launch* for both the parent coach and peer workers.

A parent coach will train the parents to deliver CM-EA. However, for training the parent coach, a web-based CM-EA training support system will be used [77]. Developed by coinvestigator [name] with support from principal investigator [name] and modified from previous web-based CM training systems, it includes modules corresponding to each CM-EA component. Within each module, sections describe CM steps, give troubleshooting tips, and provide sample scripts and video examples. Each module can be completed in 1 to 2 web-based sessions depending on the activities involved (eg, some sessions include homework), and it takes the average user <8 hours to complete all modules. The website’s navigation guides users through the modules, and a passing score of 80% is required on a multiple-choice test to access the next module. Trainees failing to pass a test are able to rereview the module or access support from a CM-EA expert and can take the posttests to achieve a passing score. Furthermore, the team will adapt written training materials and develop a 3-day virtual CM-EA training for the parent coach, which will include *Launch* services review, role-playing, and other active training exercises that the team has successfully used across numerous research studies involving CM.

Similar web-based training protocols will be adapted with input from individuals with lived experience with SU recovery for peer workers to deliver the in-person emerging adult PRSS components. These are more straightforward because peer workers will already be trained and certified.

##### Adaptation of Adherence Instruments

The research team has developed adherence measurement tools for the delivery of CM-EA led by coinvestigator [name] as part of other related projects. The original tools were developed using methods from the Standards for Educational and Psychological Testing and Item Response Theory–based methods defined by Wilson [78]. However, the existing tools will need to be reviewed and adapted.

First, our existing observational tool for measuring CM-EA adherence among clinicians and paraprofessionals working with emerging adults will be adapted to measure CM-EA adherence among coaches working with parents. Coaches will audio record all CM-EA coaching sessions to facilitate our assessment of their adherence. Coaches will also complete a modified session checklist where they report the CM-EA skills that the parent reported implementing at home in their coaching session. Second, our observational vocational or educational skill-building adherence tool developed in a previous project (grant K23DA04861) will be reviewed to ensure that it remains relevant to this project. A self-report adherence measure will be adapted from the same project (grant K23DA04861) to capture PRSS interactions that occur when audio recording is not optimal (eg, during recreational activities such as playing basketball or frisbee). The peer workers will complete a self-report measure of adherence for every emerging adult interaction and audio record sessions as appropriate. The participating parent coach and peer workers will be asked to provide feedback on these forms as part of their qualitative interviews.

Members of the research team will code the coach and PRSS session tapes and train an additional coder in using the adapted adherence instruments to obtain observational ratings on whether the different *Launch* components were delivered with adherence. Training for coders will begin with review of the coding tools and group practice ratings. Next, coders will independently rate session tapes and review for consensus. From this process, the coding instrument and manual will be refined as needed. This process will continue until coder ratings achieve acceptable consistency (≥80% agreement). As feasibility is a major aim of this pilot project, all submitted tapes will be coded. Booster trainings will monitor and address coder drift identified through discrepancies in double coding. The steps for developing this observational coding system and training coders follow procedures that the investigators have used numerous times for adherence measurement [79] and have been a focus of a project led by coinvestigator [name] (grant MH097000). These adherence tools will also be used during supervision to monitor adherence to each protocol and provide feedback or booster trainings.

#### Aim 2

After recruitment, interested participants will meet with a research team member to complete informed consent. Then, emerging adults will complete an approximately 1-hour virtual baseline interview. On the basis of the experience of the research team, 1-hour assessments rarely present a significant response burden, but the research team will use breaks to attenuate circumstances that threaten the validity of the assessments. A stratified permuted block randomization design [80] will be used to randomize the families to one of three treatment conditions: (1) web-based CM-EA parent coaching only, (2) in-person PRSS for the emerging adult only, or (3) both web-based CM-EA parent coaching and in-person PRSS for the emerging adult. Families will receive *Launch* services for approximately 5 months. All activities with the parents will be web-based, assessments with emerging adults will be web-based, and PRSS sessions with the emerging adults will be in person. The parent coach and peer workers will track session attendance. At 6 months after the baseline, emerging adults will complete a virtual, 1-hour follow-up assessment, and parents will complete an approximately 1-hour qualitative interview (see the *Measures* section) that will also include a limited number of brief quantitative questionnaires. At the end of their participation in the project, the parent coach and peer workers will complete an approximately 1-hour qualitative interview about *Launch* services (see the *Measures* section).

#### Aim 3

We plan to conduct a series of interviews with approximately 10 pertinent payers or providers of recovery services to ensure that we have a complete list of data to be collected in a follow-up large-scale trial. The research team will use access to their national community boards as part of other funded work (grant R24DA051950) and community partners to interview administrators of provider agencies of SU recovery services as well as representatives from insurance providers or behavioral health care systems. An explicit goal of these interviews will be gathering information on types of evidence needed to promote future funding of a service package such as *Launch* or the components within *Launch*. Information gathered from these interviews will allow us to include appropriate measures in the resulting large-scale study as well as help inform a future economic evaluation aim. At the completion of the interviews with payers or providers, we will have a list of key outcomes to include in the follow-up large-scale study proposal informed by those who will be funding and providing the services in the future.

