### Analysis Plan

#### Aim 1

Aim 1 includes 2 groups of analyses. The first group is a preliminary psychometric evaluation of the adapted instruments measuring the adherence of (1) coaches training parents in the use of CM-EA and (2) standard PRSS plus vocational or educational skill building. The number of families is modest, but each will have numerous repeated measurements. The second group of analyses will determine whether coaches can train parents to deliver CM-EA and whether peer workers can deliver the combined services (ie, PRSS plus vocational or educational skill building). All data will be nested, with repeated measurements (level 1) nested within families (level 2), but the actual number of measurements will vary for each family and type of adherence. Nesting will be addressed using mixed-effects regression models. To evaluate parent training, the model will include a linear time term, which will estimate the initial level of coach adherence and test for change over time, and this will be interpreted relative to theory-based standards for acceptable training. To evaluate the delivery of PRSS plus vocational or educational skill building services, the same type of model will be performed. Combined, the results will determine whether the proposed protocols lead to the expected levels of adherence for coaches as well as peer workers, and low adherence scores will be investigated during the proposed qualitative interviews.

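### Aim 1 adherence tapes are coded by the team that trains and supervises the peer workers, and the stated double-coding checks cannot show whether the adherence level is inflated

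*Protocol article*

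**What the plan says.** All references are to the protocol article.

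- **Who adapts the training** (Aim 1: Adaptation of Training Protocols, Overview): "we will adapt our training protocols to allow for virtual training and support of *Launch* for both the parent coach and peer workers".
- **Who trains and supervises peer workers** (Peer Worker Training and Supervision): "Peer workers will be trained by the research team to use the workbook", and "Peer workers will receive supervision from the research team at least twice a month that may include reviewing adherence tools".
- **Who made the instruments** (Adaptation of Adherence Instruments): "The research team has developed adherence measurement tools for the delivery of CM-EA".
- **Who codes** (same section): "Members of the research team will code the coach and PRSS session tapes and train an additional coder in using the adapted adherence instruments".
- **Second use of the same tools** (same section): "These adherence tools will also be used during supervision to monitor adherence to each protocol and provide feedback or booster trainings".
- **Coder quality control** (same section): practice ratings, then independent ratings reviewed to consensus, continued until agreement reaches at least 80%. Discrepancies in later double coding serve to detect drift, and booster training addresses it. All submitted tapes are coded. The share to be double coded is not given.
- **What the scores decide** (Analysis Plan, Aim 1): a mixed model estimates the initial adherence level and its change over time, read against a theory-based standard. The article concludes that "the results will determine whether the proposed protocols lead to the expected levels of adherence for coaches as well as peer workers".

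**The concern.** The adherence score is the evidence on whether the training protocols work, and it is produced within the team that prepared and delivers that training. A rater who trained a peer worker, or who has already given that person feedback using the same tool, may credit a component that an outside rater would not. Every safeguard described concerns consistency: whether coders agree with each other, and whether they stay in agreement. None concerns whether the level is right. Coding every tape reduces random error but leaves a systematic error untouched.

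At stake is the level that Aim 1 compares with its standard. If that level is too high, training that needs work could be carried into the larger trial. Low scores, which are meant to be explored in the qualitative interviews, would also be seen less often.

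**Working it through.** The article gives no adherence scale, no numerical standard and no count of double-coded tapes, so there is no plan figure to reproduce. The figures below are illustrations. Every input is an assumption except the 80% agreement gate, the 48 families and the service length of about 5 months.

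**1. Leniency shared by all coders.** Let t be true adherence, L the probability that an undelivered item is credited by all coders alike, and e = 5% the independent error of each coder.

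- Credited share: m = t + (1 − t)L
- Scored adherence: m(1 − e) + (1 − m)e
- Agreement between coders: (1 − e)² + e² = 0.9025 + 0.0025 = 90.5%, whatever L is

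For t = 60%:

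| L | m | Scored adherence | Agreement |
|---|---|---|---|
| 0 | 0.60 | 59% | 90.5% |
| 0.25 | 0.70 | 68% | 90.5% |
| 0.50 | 0.80 | 77% | 90.5% |
| 0.75 | 0.90 | 86% | 90.5% |

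For t = 50% the scores run from 50% to 84%, and for t = 70% from 68% to 88%. The 80% gate is passed in every case.

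**2. Leniency tied to role.** Now suppose that the team coder credits a share L of undelivered items and the additional coder credits none. Before random error, the team level is t + (100 − t)L. With e = 5% for both coders, the mean difference shrinks by the factor 1 − 2e = 0.9. The pair disagrees in principle on d = (1 − t)L of items, so agreement is (1 − d) × 0.905 + d × 0.095.

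| t | L | Team level before error | Mean difference with error | Agreement |
|---|---|---|---|---|
| 70% | 10% | 70 + 30 × 0.10 = 73 | 0.9 × 3 = 2.7 points | 0.97 × 0.905 + 0.03 × 0.095 = 88.07% |
| 75% | 20% | 75 + 25 × 0.20 = 80 | 0.9 × 5 = 4.5 points | 0.95 × 0.905 + 0.05 × 0.095 = 86.45% |
| 70% | 30% | 70 + 30 × 0.30 = 79 | 0.9 × 9 = 8.1 points | 0.91 × 0.905 + 0.09 × 0.095 = 83.21% |

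Agreement stays above 80% here too, but the signed mean difference shows the gap. The two cases therefore differ: a team-minus-additional comparison can reveal role-based leniency, but not leniency that all coders share.

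**3. Precision of the mean difference.** Treating tapes as independent, the half-width is 1.96 × SD/√n.

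- n = 80, SD = 10 points: 1.96 × 10/√80 = 2.2 points
- n = 60, SD = 15 points: 1.96 × 15/√60 = 3.8 points

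These are too narrow. Tapes are nested in families, and the article describes one parent coach, so the coaching tapes may all come from one provider. A variance inflation of D multiplies each half-width by √D. The smallest difference above (2.7 points) could not be relied on to stand out.

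**4. Level and slope.** A fixed number of points added to every score raises the level and leaves the time slope unchanged. If instead a fixed fraction L of undelivered items is credited, a true slope is multiplied by 1 − L: it is flattened, not created. A spurious rise would need leniency that grows over time.

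**The case against.** The strongest objection is that this rests on silence in a condensed article. The text names the research team, not individuals, and nowhere says that the person who supervises a peer worker also codes that worker's tapes. Coder assignment and masking usually sit in a coding manual, and the article mentions one that is not shown. That stands as a limit on the claim. It does not remove the point, because the coding section does state who codes, how coders are calibrated and what double coding is for, and the level is unprotected by those stated choices.

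A reader might infer more than the documents support:

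- **Supervisors score their own trainees.** The article shows only that nothing stated prevents it. For the parent coach the overlap is thinner still: supervision by the research team is named for peer workers, and part of the coach's training is web modules with a test.
- **The Aim 1 level is biased upward.** No data show this. Supervisors could equally be stricter than outsiders.
- **Double coding can serve no purpose other than drift.** Drift is the only use stated; other uses are not ruled out.
- **A miss will be turned into a pass.** No cut-off is given, the study tests objectives and not formal hypotheses, and no progression rule is tied to this score.

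Two objections to the remedy also stand. The additional coder is trained by the team and calibrated to consensus with it, so a zero difference would not show that scores are accurate. A blanket ban on team coding could also be costly. With equal allocation (assumed), 48/3 = 16 families per arm, so 32 families receive coaching. About 20 weekly sessions over some 5 months gives up to 32 × 20 = 640 coaching tapes, before any peer-worker tapes. Placing all of these on one coder may be unworkable.

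**Conclusion.** The point holds as a risk. The team that adapts the training and trains and supervises the peer workers also codes the tapes, no stated rule separates those roles for a given provider, and the stated checks measure consistency and not level. Aim 1 then draws its conclusion from that level.

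The possible size depends wholly on assumptions. In the illustrations, role-based leniency adds about 3 to 9 points before coder error, and strong shared leniency adds up to 27 points (59% to 86% at 60% true adherence), all with agreement above 80%. The documents do not show that any such leniency exists, or that the same individuals hold both roles. The conclusion concerns the level; a constant shift would not affect the slope. This is a worthwhile, inexpensive improvement to a pilot measure, not a flaw that invalidates the study.

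**What to change.** 1. Where staffing allows, do not assign a tape to a coder who trained or supervises that provider. If roles are already separated this way, one sentence saying so settles this part.
2. Draw the double-coded tapes at random. Pair a team member with the additional coder, and state that this coder has no training or supervision role and is masked to supervision feedback.
3. Analyse the independent ratings made before any consensus discussion. Report the mean difference (team minus additional coder) beside the Aim 1 level, with a 95% CI that allows for clustering by family and provider.
4. If the difference is material, show the Aim 1 level from the additional coder's ratings as a sensitivity result, not as an automatic replacement.
5. State that leniency shared by all team-trained coders would remain undetected.

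The cost is some coding hours moved to the additional coder and one extra summary. The double coding and that coder are already in the plan, and no treatment procedure changes.

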### Measures

#### Emerging Adult Measures

Primary outcomes for emerging adults include the emerging adults’ perceptions of *Launch* acceptability, appropriateness, and feasibility; the emerging adults’ satisfaction with *Launch* services; and a qualitative interview. Emerging adult perceptions of implementation-related outcomes will be measured using the 3 implementation outcome measures validated in the study by Weiner et al [81]: the Acceptability of Intervention Measure, Intervention Appropriateness Measure, and Feasibility of Intervention Measure, which together total 12 items scored on a Likert-type scale taking respondents approximately 4 minutes to complete. This combined measure has demonstrated good internal consistency (Cronbach α=0.87 to 0.89) and test-retest reliability (0.73 to 0.88) [81]. Satisfaction with *Launch* services will be measured using the 8-item Client Satisfaction Questionnaire (CSQ-8) [82], adapted to reflect receipt of *Launch* services. The CSQ-8 is an 8-item measure using a 4-point Likert-type scale, with higher scores indicating greater satisfaction, and takes approximately 3 minutes to complete [82]. Finally, the emerging adult qualitative interview (approximately 30 to 60 minutes) will delve deeper into emerging adult perceptions of the acceptability, appropriateness, and feasibility of *Launch* as well as the research protocol and ask emerging adults to describe the impact of receiving *Launch* services and any impacts (positive or negative) on the parent–emerging adult relationship. All primary outcomes for emerging adults will be measured at the end of the study period (6 months after baseline).

Secondary outcomes for emerging adults include the emerging adults’ relationships with their peer workers if receiving PRSS, the emerging adults’ relationship with their parents, SU, emerging adult PRSS session attendance (for those randomized to this condition), quality of life, nonstudy medical service use, self-efficacy, recovery capital, history of medications, and research values. Emerging adults’ relationships with their peer workers and their parents will be measured using adapted versions of the short form of the Dual-Role Relationship Inventory [83], a validated measure that assesses whether provider-client relationships are perceived as firm, fair, and caring by participants; consists of 9 items scored on a 7-point Likert-type scale ranging from *never* (1) to *always* (7); and takes approximately 3 minutes to complete. SU among emerging adult participants will be measured at baseline and at follow-up using self-reported measures only. The *DSM-V* Substance Use Checklist [73] measures past–12-month SU as a *yes* or *no* response to 8 substance categories—alcohol, cannabis, hallucinogens, inhalants, opioids, sedatives, hypnotics, or anxiolytics, stimulants, and an “other” category—but does not ask about frequency. For each substance type, 11 yes or no items measure *DSM-V* SU disorder symptom endorsement, and each question set takes approximately 2 minutes to complete (ie, if an emerging adult endorses 2 substances, then the total *DSM-V* checklist time will be approximately 4 minutes). Endorsing ≥2 symptom items qualifies as an SU disorder for that specific substance, with 2 to 3 symptoms constituting a mild SU disorder, 4 or 5 symptoms constituting a moderate SU disorder, and ≥6 symptoms endorsed constituting a severe SU disorder. A second SU measure from the Global Appraisal of Individual Needs [84] and the Justice Community Opioid Innovation Network (JCOIN) Core Measures [85] will be used to ask about frequency (number of days) of using different substances in the past 30 days as well as number of abstinent days, past–30-day overdose or receipt of naloxone, and symptoms of SU disorder. The Global Appraisal of Individual Needs SU measure consists of 53 closed-ended items and 1 open-text item and takes approximately 10 minutes to complete. Finally, the Polysubstance Assessment Tool [86,87] will be used to assess poly-SU in the past 30 days and main motivation for use. This measure uses branching logic, consists of 2 ranking items and 6 closed-ended items (checklists of substances used and combinations of use), and takes approximately 5 minutes to complete. PRSS session attendance will be tracked by the peer worker. Quality of life will be measured using the Patient-Reported Outcomes Measurement Information System (PROMIS)–29+2 Profile version 2.1 [88], a 31-item measure of quality of life across 7 domains: physical function, anxiety, depression, fatigue, sleep disturbance, social participation, pain interference, pain intensity, and cognitive function. The 31 items are multiple choice and scored on a 5-point Likert-type scale for all items except for a 10-point general pain level ranking item and take approximately 10 minutes to complete. Importantly, the PROMIS-29+2 Profile version 2.1 can be used with a scoring method called PROMIS-Preference (PROPr) to calculate a utility weight, which is key to economic evaluation methods such as cost-effectiveness analysis, thereby ensuring that a future large-scale study of *Launch* can integrate an economic evaluation aim. This version of the PROMIS is used as part of the JCOIN Core Measures [85], as is the measure of nonstudy medical service use.

Self-efficacy will be measured using the Brief Abstinence Self-Efficacy Scale [89] at baseline and the 6-month follow-up. The Brief Abstinence Self-Efficacy Scale consists of 11 items scored on a 5-point Likert-type scale [89] and takes approximately 4 minutes to complete. Recovery capital will be measured using an emerging adult–specific measure under development by members of the study team and collaborators at baseline and the 6-month follow-up. The emerging adult recovery capital measure uses 49 items scored on a 4-point Likert-type scale, with higher values meaning higher recovery capital, and also includes 3 preliminary short-answer questions, totaling 52 items and approximately 17 minutes to complete. Medication history will also be drawn from the JCOIN Core Measures and ask about current medication use only as well as lifetime prescription of a medical marijuana card and will be asked at both baseline and follow-up. The medication history measure consists of 5 items and takes approximately 2 minutes to complete. The Emerging Adult Research Values Exercise [90] was developed by members of the study team and collaborators and will be administered at the end of the baseline interview only. The emerging adult will be asked about why they were willing to participate in the research, choosing from as many of the possible response options available as they wish to select. Response options include reasons such as “to get the study incentives” and “to help other people like me.” Participants can then choose their top 3 reasons from among the reasons they selected. As the final step of the research values exercise, the emerging adult will be asked how likely they are to meet with the research team for follow-up and whether the researchers can do anything to increase that likelihood.

Demographics will also be collected at baseline, with some items that are changeable (eg, housing, employment, or educational status) repeated at the 6-month follow-up. The demographics measure used has been adapted from Brown [91] and is from the JCOIN Core Measures [85], with updated demographic response options from the Justice and Emerging Adult Populations Initiative’s resource on using destigmatizing language [92]. The final demographic instrument consists of 33 items and takes approximately 6 minutes to complete.

